## Abstract

**Background:**

Mosquito-borne arboviruses, like dengue virus, continue to cause significant global morbidity and mortality, particularly in Southeast Asia. When the infectious mosquitoes probe into human skin for a blood meal, they deposit saliva containing a myriad of pharmacologically active compounds, some of which alter the immune response and influence host receptivity to infection, and consequently, the establishment of the virus. Previous reports have highlighted the complexity of mosquito vector-derived factors and immunity in the success of infection. Cumulative evidence from animal models and limited data from humans have identified various vector-derived components, including salivary components, that are co-delivered with the pathogen and play an important role in the dissemination of infection. Much about the roles and effects of these vector-derived factors remain to be discovered.

**Methods/Design:**

We describe a longitudinal, pagoda (community)-based pediatric cohort study to evaluate the burden of dengue virus infection and document the immune responses to salivary proteins of *Aedes aegypti*, the mosquito vector of dengue, Zika, and chikungunya viruses. The study includes community-based seroprevalence assessments in the peri-urban town of Chbar Mon in Kampong Speu Province, Cambodia. The study aims to recruit 771 children between the ages of 2 and 9 years for a three year period of longitudinal follow-up, including twice per year (rainy and dry season) serosurveillance for dengue seroconversion and *Ae. aegypti* salivary gland homogenate antibody intensity determinations by ELISA assays. Diagnostic tests for acute dengue, Zika and chikungunya viral infections will be performed by RT-PCR.

**Discussion:**

This study will serve as a foundation for further understanding of mosquito saliva immunity and its impact on *Aedes*-transmitted arboviral diseases endemic to Cambodia.

**Trial registration:**

NCT03534245 registered on 23 May 2018.

## Background

Recently, important *Aedes* mosquito-borne viruses such as chikungunya (CHIKV), yellow fever, dengue (DENV), and Zika (ZIKV) have re-emerged and caused public health alarm on a global scale [1–3]. Accumulating evidence in animal models suggest that mosquito saliva proteins (MSPs) increase the infectivity of these arboviruses [4–10]. Despite the evidence that mosquito saliva overall facilitates infection, relatively few proteins have been identified as immunomodulatory. *Aedes aegypti* saliva has over 20 unique abundant secreted proteins, most of unknown function [11]. Further complicating our understanding, arthropod salivary components are highly diverse with some proteins facilitating infection, while others may impede viral infection when tested in isolation [12–14]. Moreover, viral infection and dissemination differs between needle-inoculated *versus* arthropod-delivered infection models in mice, hamsters, beagles and primates [6, 7, 15, 16].

The relationship between mosquito saliva reactivity and clinical disease thus needs further investigation. An *Aedes aegypti* N-terminus 34-kDa salivary peptide of unknown function is a known marker of *Aedes* spp. mosquito exposure in humans, but depends on the location and timing of the exposure [17]. Less information is available on how salivary proteins may impact risk of arboviral infection in humans. Indeed, the few human studies devoted to disease development have been limited by power, retrospective design, or convenience sampling [18, 19]. To address some of the key knowledge gaps, we have established a protocol to study dengue seroprevalence and *Aedes aegypti* saliva reactivity *via* a prospective cohort of at-risk children in a country endemic to multiple *Aedes*-transmitted diseases.

Cambodia, a country with an estimated population of approximately 16 million, has multiple mosquito-borne diseases caused by various malaria parasites and DENV, CHIKV, ZIKV, and Japanese encephalitis virus (JEV) [20]. The risk of arboviral disease may be increasing in the next decade as the Cambodian urban population is expected to double before 2030 [21]. Rapid urbanization, congestion, land-use change and flooding may further contribute to increased risk in mosquito or vector-borne diseases in this region [22].

With regard to *Aedes*-transmitted infections, DENV is most common in Cambodia and is highly endemic with year-round transmission, peaking from July to November when rainfall is at its highest. Transmission is highly focal but is found in both rural and urban areas in Cambodia [23, 24]. The National Dengue Control Programme (NDCP) has a pediatric hospital-based syndromic surveillance system across the country. At five sentinel sites, clinically suspected cases are sent to Pasteur Institute to confirm DENV infection *via* RT-PCR detection of the virus [20]. Epidemiological studies otherwise rely upon reports of clinically diagnosed dengue-like cases (occasionally confirmed by SD Bioline Dengue Duo rapid tests when available) from hospitalized children under 16 years of age, with little assessment or data in older adults who are less likely to seek care. In Cambodia, average DENV incidence appears to be highest in those under 7 years of age (approximately 41 cases per 1000 person-seasons in one active community-based surveillance study from 2006 to 2008) [24]. Given its reliance on a clinical reporting system, national DENV incidence data likely underestimates true DENV incidence in Cambodia by 3 to 27-fold, per capture-recapture analyses [25]. Among other arboviruses, CHIKV outbreaks are occasionally documented in Cambodia, e.g. one village in Kampong Speu Province experienced a 44% attack rate in 2012 [26]. ZIKV transmission is uncharacterized and may sporadically occur in Cambodia [20].

Considering the vector abundance of *Aedes* mosquitos and the presence of multiple *Aedes*-transmitted viruses in Cambodia, we chose to establish a prospective pediatric cohort using local pagodas (religious temples) for community recruitment and follow-up. This study protocol aims to define the seroprevalence of antibodies to both DENV and *Aedes aegypti* salivary gland homogenate (SGH), describe the epidemiology of symptomatic *Aedes*-transmitted infection in children in this community, characterize the demographic and entomological factors that contribute to DENV infection, and establish the magnitude of human antibody response to *Ae. aegypti* saliva. These data will establish the groundwork on which to better understand the roles of vector-borne determinants of arboviral infection.

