## Methods/Design

### Study design and objectives

This is a prospective pagoda (community)-based cohort study with the following primary objectives: (i) to determine the seroprevalence of antibodies indicating previous *Aedes*-transmitted DENV infection in children; and (ii) to describe the seropositivity to *Aedes* salivary gland homogenate (Table 1). The study will screen up to 1200 and recruit up to 771 children aged 2–9 years for study enrollment and then follow them longitudinally for three years. The study is being conducted over three years given the high rate of variability in *Aedes*-transmitted disease transmission from year to year. The study is focused on children aged 2–9 years of age as they have the greatest burden of disease in Cambodia and thus offers comparability to other pediatric DENV cohorts [23–25, 27].

**Table 1 Tab1:** Study objectives and endpoints

Objectives	Endpoints	Justification for endpoints
• Primary		
Describe the seroprevalence of dengue infection (both symptomatic and inapparent) in children aged 2–9 years-old in Kampong Speu	Prevalence of symptomatic and inapparent dengue infection (serotypes 1–4) as detected semiannually *via* ELISA (binary outcome present/absent) over a 3-year period in Kampong Speu in children aged 2–9 years-old	Detailed knowledge of dengue seroprevalence and transmission season variability will help establish an epidemiological foundation to prepare for larger future studies such as disease incidence studies or vector interventional trials
Describe the seroprevalence of reactivity to *Ae. aegypti* salivary gland proteins in children aged 2–9 years-old in Kampong Speu	Prevalence of *Ae. aegypti* salivary gland homogenate reactivity as detected by ELISA assay (binary outcome present/absent) during wet and dry seasons over a 3-year period in Kampong Speu in children aged 2–9 years-old	Characterizing the *Ae. aegypti* salivary protein reactivity profile in Cambodians is the first step prior to assessing how *Ae. aegypti* saliva exposure modulates disease in humans
• Secondary		

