### Clinical and laboratory procedures

At screening and enrollment, children and their guardians undergo informed consent and child identify verification (by village chief if child unable to verbalize the name of their guardian). Baseline demographics are collected, including: sex, age, residential address, dengue risk factors (e.g. number of domestic water containers at household, larvicide use), bednet use, past medical history, drug allergies, and any current or previous (within past month) use of over-the-counter, prescription, or traditional remedies. Participants undergo a targeted exam that includes vital signs, height and weight.

At baseline, trained phlebotomists collect 8 ml of peripheral blood in a heparin tube for peripheral blood mononuclear cell processing for future cellular assays and 6 ml in a serum separator tube (SST) for detection of dengue-specific antibodies using the PanBio Indirect IgG ELISA kit. For the serum samples that are found to be positive for DENV IgG, a plaque reduction neutralization test (PRNT) will be performed in order to determine the antibody titer to each of the four DENV serotypes. This will establish a baseline profile for each participant.

At semi-annual follow-ups, participants will undergo venipuncture of 8 ml in a serum separator tube for follow-up dengue antibody assessment *via* ELISA, and for those who have seroconverted to positive since baseline, follow-up PRNT assays will be done. At the first semi-annual follow-up, additional whole blood of up to approximately 2 ml will be taken for alpha-thalassemia typing and point-of-care hemoglobin testing. At the final visit of the study, 8 ml of whole blood in a heparin tube will again be taken for PBMC processing for future cellular assays.

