### Statistical analysis

The primary endpoints will be defined as:(i)Seropositivity to DENV1-4 per indirect IgG ELISA (with plaque reduction neutralization assays performed as necessary to confirm inapparent dengue infections)(ii)Seropositivity to *Ae. aegypti* salivary gland homogenate

Seroprevalence to each dengue serotype will be presented as a proportion for each timepoint. Unadjusted and adjusted logistic regression models will be performed evaluating the relationship between time and seroprevalence, with adjustments for age, year or season of collection, and socio-economic conditions (e.g. type of housing). Further, the seroconversion rate and change in the immune status will be determined by participants and separated by age group during the study period. Quasi-Poisson regression models will be fit to evaluate the relationship of age, year, socio-economic conditions (e.g. type of housing) to the primary endpoints of dengue infection or *Ae. aegypti* salivary gland homogenate seropositivity and to estimate prevalence ratios.

Because seroconversion to *Ae. aegypti* salivary gland homogenate is measured repeatedly on subjects over three years during wet and dry season, a single subject may be negative for seroconversion at one time, and positive at a later time. This will allow us to perform our secondary objective to evaluate the kinetics of the antibody response. Given these changing values, seroprevalence to *Ae. aegypti* salivary gland homogenate will be presented as proportion representing point prevalence for each season in each year of the study.

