## Discussion

Cambodia is rapidly changing and its urban population is projected to double in the next decade [21]. While dengue is transmitted in both rural and urban areas of Cambodia, an increase in urban and peri-urban slum-dwelling residents, paired with poor sanitation practices and flooding, raises the risk for arboviral disease outbreaks [22, 23]. In order to allocate scarce resources, the Ministry of Health needs access to high-quality data that can provide guidance regarding dengue epidemiology of both inapparent and symptomatic infection, individual risk factors such as water container numbers and larvicide use, characterization of the *Aedes* vector and its abundance in terms of traditional *Stegomyia* indices as well as anti-saliva antibodies that describe direct human-vector contact. Access to these baseline cohort data may aid in national decisions regarding effectiveness and implementation of vector control measures, epidemic forecasting, and/or arboviral disease risk assessments in the future.

In addition to providing important public health information on dengue and its mosquito vector, the study aims will contribute to the epidemiologic groundwork necessary to elucidate the relationship between arboviral disease development and anti-*Ae. aegypti* mosquito salivary peptide antibodies. The sialotranscriptome of *Ae. aegypti* has been characterized [38], and some immunomodulatory proteins have been identified. One 34-kDa salivary protein of unknown function was shown to: (i) suppress antimicrobial peptide secretion by keratinocytes; and (ii) inhibit type 1 IFN expression as well as its regulatory factors [39]. Another salivary protein, CLIPA3 protease, promotes DENV replication and dissemination *via* cleavage of extracellular matrix proteins, liquefying the dermal layer to theoretically permit interaction between virions and local immune cells that will subsequently migrate to draining lymph nodes to enhance DENV infectivity [10]. Recently, a 15-kDa salivary protein called LTRIN augmented ZIKV pathogenesis in *Ifnar -/-* mice by interfering with lymphotoxin receptor signaling, a communication link between the lymph nodes and surrounding stromal environment [9]. However, many mosquito salivary peptides remain unidentified and functionally uncharacterized.

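### The stated regression of demographic and socio-economic factors on DENV infection uses cumulative IgG prevalence, so it cannot show which changeable factors contribute to new infection; a seroconversion model should be added.

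*Protocol article*

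**What the plan says.** - **Aim.** The Background section sets out to "characterize the demographic and entomological factors that contribute to DENV infection".
- **What the serology measures.** The first primary objective (Study design and objectives) is "to determine the seroprevalence of antibodies indicating previous *Aedes*-transmitted DENV infection in children". The endpoint under Statistical analysis is "Seropositivity to DENV1-4 per indirect IgG ELISA", with neutralisation tests as needed to confirm inapparent infection.
- **The factor model.** Under Statistical analysis: "Quasi-Poisson regression models will be fit to evaluate the relationship of age, year, socio-economic conditions (e.g. type of housing) to the primary endpoints", "and to estimate prevalence ratios". The logistic models there also take seroprevalence as outcome. The DENV seroconversion rate is to be reported by age group; no regression is attached to it.
- **When factors are recorded.** Clinical and laboratory procedures lists, among the enrolment items, "dengue risk factors (e.g. number of domestic water containers at household, larvicide use), bednet use". Mosquito surveillance describes larval surveys of about 800 randomly chosen houses in each rainy season of the study.
- **Intended use.** The Discussion says the Ministry of Health needs data on "individual risk factors such as water container numbers and larvicide use", among other things.
- **Other disease models.** Statistical analysis also plans spatial models of risk of disease, and an exploratory incidence model of composite arboviral disease by saliva seroconversion.

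**The concern.** A factor contributes to infection only if it was present before the infection. A child who is IgG-positive at enrolment was infected at some unknown earlier time, up to nine years before. That child stays positive at every later round and counts each time as an outcome of conditions recorded afterwards. Infections that could have followed the recorded factor are thus diluted by infections that could not. Adjusting for age does not restore the time order.

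The cohort does observe what the aim needs: each child is retested every dry and wet season, and converters have follow-up neutralisation tests. As written, that information is only tabulated by age group. At stake is the risk-factor aim. A changeable factor with a real effect could be reported as weak or absent.

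**Working it through.** **The plan's own figure.** The article gives no figure for this regression. Its one calculated figure is the sample size. With 701 children the average exact 95% interval at a true rate of 0.5 has length 0.0753, which rounds to the stated 0.075, and 701 × 1.10 = 771. I take 701 evaluable children, about 350 in each half.

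**Inputs from the article.** Entry ages 2–9 in four equal age bands; three years of follow-up; acute dengue incidence of 13.7–58 per 1000 person-seasons (Sample size calculation).

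**Assumptions.** Force of infection L is constant. One season per year gives L = 0.014 to 0.058. That counts acute cases only and inapparent infection would raise it, so I range L up to 0.15. IgG is lifelong, and ages at entry are 2.5, 3.5, …, 9.5 in equal shares. Half the children hold a factor with hazard ratio 2 and mean hazard L, so the hazards are 4L/3 and 2L/3.

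**Formulas.**
- Baseline prevalence: B = mean of 1 − exp(−L·a) over entry ages a. The share still negative is S = 1 − B.
- Factor acting only during the study, last-visit prevalence at hazard h: mean of 1 − exp(−L·a − 3h).
- Pre-enrolment share: B divided by the average last-visit prevalence of the two groups.
- Three-year seroconversion risk in baseline-negatives: 1 − exp(−3h).
- Stable, lifelong factor, baseline prevalence: mean of 1 − exp(−h·a).
- Power: Φ(|p1 − p0|/SE − 1.96), with SE = √{[p1(1 − p1) + p0(1 − p0)]/n}; n = 350 per group for prevalence and 350·S for seroconversion.

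**Factor acting during the study only, true hazard ratio 2**

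| L per year | 0.014 | 0.05 | 0.10 | 0.15 |
|---|---|---|---|---|
| Baseline prevalence B | 0.080 | 0.254 | 0.437 | 0.569 |
| Last-visit prevalence, with/without factor | 0.130/0.105 | 0.389/0.325 | 0.622/0.539 | 0.763/0.681 |
| Share infected before enrolment | 68% | 71% | 75% | 79% |
| Prevalence ratio | 1.23 | 1.20 | 1.15 | 1.12 |
| Power, last-visit prevalence | 17% | 43% | 61% | 69% |
| Seroconversion risk, with/without factor | 0.0545/0.0276 | 0.181/0.095 | 0.330/0.181 | 0.451/0.259 |
| Risk ratio | 1.97 | 1.90 | 1.82 | 1.74 |
| Negatives per group (350·S) | 322 | 261 | 197 | 151 |
| Power, seroconversion | 40% | 82% | 93% | 94% |

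If L is instead the hazard without the factor and 2L the hazard with it, the prevalence ratio runs from 1.31 (L = 0.014) to 1.14 (L = 0.15).

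**Stable factor such as housing, true hazard ratio 2**

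| L per year | 0.014 | 0.05 | 0.10 | 0.15 |
|---|---|---|---|---|
| Baseline prevalence, with/without factor | 0.105/0.054 | 0.322/0.179 | 0.529/0.322 | 0.666/0.437 |
| Prevalence ratio | 1.94 | 1.80 | 1.64 | 1.53 |
| Power, baseline prevalence | 70% | 99% | over 99% | over 99% |
| Power, seroconversion in negatives | 40% | 81% | 92% | 93% |

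**Events for the added model.** At L = 0.014: 322 × (0.0545 + 0.0276) ≈ 26 over three years. At L = 0.15: 151 × (0.451 + 0.259) ≈ 107.

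**The case against.** *The article has other disease models.* This is true, and a reader might wrongly infer that the prevalence model is the only DENV regression. The spatial models relate geographic data to risk of disease, and the exploratory model relates incidence of composite arboviral disease to saliva seroconversion. The Discussion also promises demographic and behavioural data in models, but in the context of interpreting saliva reactivity. None of these states new DENV seroconversion as the outcome with demographic, household or entomological factors as predictors.

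*The factors most affected are not in the stated model.* That model names age, year and socio-economic conditions, with housing as the example. Water containers, larvicide, bednets and larval indices do not appear. This stands: the ratios of 1.23 to 1.12 show what would happen if the stated approach were applied to such factors. For housing, prevalence does well. It also means that the entomological half of the aim rests on the spatial models alone.

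*A prevalence ratio below the hazard ratio is a different estimand, not an error.* That is right for stable factors. For changeable ones the difference also reflects infections that came before the recorded factor.

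*Effects could reverse.* A reader might infer this if families adopt a measure after a child has dengue. Cumulative prevalence alone does not reverse an effect: over L = 0.014 to 0.20, a practice with hazard ratio 0.7 during follow-up gives 0.91 to 0.96. If 30% of families use it and use is 10 points higher where a child was already infected, the ratio becomes 1.21 to 1.03. The article reports no such change in behaviour, so this is only a possibility.

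*The primary objectives are descriptive, and the Discussion says the study is not powered for acute incidence.* Both statements are correct. They limit the weight of the point. But seroconversion includes inapparent infection, and the article itself fixes the outcome and effect measure of the factor model, so the mismatch with the aim is not mere condensation.

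**Conclusion.** The concern holds for factors that change over time, and for the aim of identifying what contributes to DENV infection. With L between 0.014 and 0.15 per year, about 68–79% of last-visit positives predate enrolment, and a during-study hazard ratio of 2 appears as about 1.23 to 1.12. No stated model relates new DENV seroconversion to factors measured beforehand. For stable factors the prevalence model is adequate and more powerful (70% to over 99%, against 40–93%). The seroprevalence estimates themselves are not in question.

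The sizes rest on a constant force of infection, lifelong IgG, equal age shares and a factor held by half the children. The article gives no ratio of inapparent to symptomatic infection, so L is a range and not an estimate.

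**What to change.** Under Statistical analysis, keep the prevalence models as description and for stable factors. Add a model of first DENV IgG seroconversion, supported by the neutralisation tests already planned, per interval among children IgG-negative at its start. Use complementary log-log or person-time Poisson regression with age and interval. Take predictors recorded beforehand: the enrolment household items and the preceding rainy season's larval index for the child's area. State that prevalence ratios for changeable behaviours will not be read as contributing factors.

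The cost is analysis work on samples already planned, with four limits to state:
- The model describes first infections only.
- Household behaviours are documented only at enrolment, so later changes are missed.
- Larval indices come from sampled houses and must be assigned to children by area.
- At the low end of the documented incidence there would be about 26 events and about 40% power for one balanced factor, so only a few pre-chosen covariates can be supported.
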